## Abstract

**Introduction:**

To minimize the risk of developing foot-ulcers, persons with diabetes are given the advice to daily inspect their feet and to apply skincare formulations. However, commercially available skincare products have rarely been developed and evaluated for diabetes foot care specifically. The primary aim of this randomized controlled trial (RCT) is to evaluate the effects in reducing foot xerosis in persons with diabetes without foot-ulcers using two skincare creams containing different humectants (interventions) against a cream base non-humectant (comparator). Secondary outcomes are to evaluate differences on skin barrier integrity, low-molecular weight biomarkers and skin microbiota, microcirculation including transcutaneous oxygen pressure, degree of neuropathy, and HbA1c between intervention-comparator creams.

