#### Sample size estimation

2.2.4

This is a superiority RCT, where either of the intervention creams is hypothesized to be superior to the comparator cream in reducing XSS score during a four-week application period. To be able to prove this hypothesis, a total of 98 participants, 39 persons with diabetes in each arm for analysis, is needed, which is based on the following: A change in XSS score ≤1 is not regarded clinically important. The estimated intra-individual standard deviation for the difference in XSS score is 2.0. With 80 % power, two-tailed significance of 2.5 % in every arm, 39 evaluable study persons is needed in every arm, a total of 78 persons. If 20 % of persons are estimated not to be fully evaluable, sample size increases to 98 (78/0.8).

The following formula will be used to calculate the number of patients needed in each part of the trial [15,16] (N = number of fully evaluable patients in each part of the trial):$$N=\frac{\sigma_{d}^{2}\times {\left(\lambda_{\alpha }+\lambda_{\beta }\right)}^{2}}{\Delta^{2}}$$In the formula above σ_d_ is the standard deviation for the difference between the change in each treatment, Δ is the difference to detect between the treatments (a difference of at least 1 is assumed to be clinically relevant), λ_x_ is the x:th percentile of the standardized normal distribution. As the test is two-sided and the significance level should be 0.0250 (in order to keep the family-wise type I error at 5 % and there are two comparisons: Canoderm® versus Decubal® and Oviderm® versus Decubal) then λ_α_ = 2.1414. If the power is 80 % then λ_β_ = 0.8416 and if the power is 90 % then λ_β_ = 1.2816.

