##### Secondary outcomes

2.3.1.2

The secondary outcomes are supporting evidence of differences in efficacy of creams on skin barrier integrity, and changes in health-related quality of life during the study period. Skin barrier integrity and hydration will be obtained by non-invasive biophysical measurements as follows.•Trans epidermal water loss (TEWL) is a key indicator of the barrier function of the stratum corneum (SC). Elevated TEWL typically indicates a compromised skin barrier, while lower TEWL is associated with good SC barrier properties and healthy skin [24].•Skin hydration by measurement of skin impedance (skin resistance and skin capacitance). It is well-known that maintaining healthy skin relies heavily on adequate skin hydration [25]. Standard methods for assessing skin hydration involve measuring the skin's electrical properties, which vary with the skin's water content. In this work, the skin hydration will be assessed by measuring the resistance and capacitance by electrical impedance spectroscopy [26]. Increased skin capacitance (increased dielectric constant of skin) indicates higher skin hydration; thus healthier skin barrier [26].•Skin surface pH provides an indication of host-microbiota interaction. Acidic pH value (*e.g.*, pH 5.5) is usually related to the dominance of commensal bacteria on the skin. Shifting skin surface pH towards basic values (*e.g.*, pH 6.8) might indicate an increased inhabitance of skin by pathogenic microbiota [27].•Health related quality of life assessed with EuroQoL 5 level (EQ-5D-5L) instrument.

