### Statistical analysis

2.5

The primary analysis principle applied will be the intention-to-treat. All statistical analysis and data management will be performed using SPSS for Windows, version 28.0 (IBM, Armonk, NY, USA). Measurements, such as XSS score, TEWL, pH, impedance, abundance of the biomarkers will be used as continuous variables and treatment with the creams, gender, and patients grouping parameters will be used as categorical variables. Descriptive statistics such as number of participants, mean, median, standard deviation, minimum and maximum values will be summarized and tabulated. XSS score will be independently evaluated by a random sample of twenty photographs by a second dermatologist, for validation purposes, to be able to assess inter-rater reliability by calculating intraclass correlation with 95 % confidence intervals. The primary outcome of the study is to compare the change in XSS score from baseline until the end (4 weeks) due to treatment with moisturizing creams vs a comparator product. Prior to analysis of the XSS differences between the treatment groups, the distribution of the data will be tested for normality by performing Shapiro-Wilk and Kolmogorov-Smirnov tests, as well as inspecting quantile-quantile (QQ) plots. Homogeneity of variances will be tested by performing Levene's test. Comparison between two related groups, *e.g.*, application of the formulation on the left and right foot, will be done by paired two-sample *t*-test, whereas for unrelated two groups two-sample *t*-test will be performed. When neither homogeneity of variances nor assumption of normality will be fulfilled, a non-parametric Wilcoxon rank sum test will be applied. In case of comparison between more than two groups, *e.g.*, the effect of three creams, one-way ANOVA with multiple comparisons (Tukey's test) will be used. Alternatively, if assumptions of normality or homogeneity of variances will not be fulfilled, non-parametric Kruskal Wallis test will be performed. The effect of covariables, *e.g.*, age, on main effect, *e.g.*, XSS change upon the treatment with the cream, will be tested by performing ANCOVA analysis. To seek for the measurements capable to explain and predict the effectiveness of the diabetic foot treatment with different creams more complex statistical analysis will be performed. Principal component analysis (PCA), multiway ANOVA and mixed models, and multiple regression analysis and model selection will be performed on the data collected. Level of statistical significance was set to p<0.05.

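### The flat p<0.05 rule in section 2.5 leaves the supporting outcomes without error control, although section 2.2.4 protects a 5 % family-wise rate for the two XSS comparisons

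*Protocol article*

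**What the plan says.** Three parts of the protocol article bear on this point.

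- **Error control (section 2.2.4, Sample size estimation).** Each arm's XSS comparison is tested at two-sided 0.025, "in order to keep the family-wise type I error at 5 % and there are two comparisons". No other outcome is mentioned there.
- **Significance rule (section 2.5, Statistical analysis).** XSS, TEWL, pH, impedance and biomarker abundances are listed together and share the same tests. The section also plans a search for predictors of treatment effect, in which "multiple regression analysis and model selection will be performed on the data collected". It ends: "Level of statistical significance was set to p<0.05". No outcome is exempted. The only multiplicity method is Tukey's test when more than two groups are compared.
- **Role of the other outcomes.** Section 2.3.1.2 says: "The secondary outcomes are supporting evidence of differences in efficacy of creams on skin barrier integrity". It lists TEWL, impedance (resistance and capacitance), pH and EQ-5D-5L without ranking them. The abstract draws the secondary set more widely: "Secondary outcomes are to evaluate differences on skin barrier integrity, low-molecular weight biomarkers and skin microbiota", followed by microcirculation, neuropathy and HbA1c. The body of section 2.3.1.2 brings those further items in as assessments that support the outcomes.

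Section 2.4 and Table 2 schedule TEWL, hydration and pH at day 14 and day 28. The four-week endpoint is fixed for xerosis; no text fixes a lead visit for the barrier measures.

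**The concern.** The article recognises that two comparisons, one per arm, call for a stricter level than 0.05, and it applies that to XSS. The same two comparisons recur for every barrier measure, yet each is judged at 0.05. More measures and possibly a second visit add to the count, and biomarker and microbiota abundances add an unspecified number of further tests. Ordinary p-values from models built by selection do not hold their nominal level at all.

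What is at stake is how far a significant supporting result can be trusted. With no lead measure or visit named, a chance finding on one of several barrier measures could be presented as backing for a humectant cream, even beside a null XSS result. Read literally, the sentence in section 2.5 also covers XSS and so conflicts with the 0.025 per arm in section 2.2.4.

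**Working it through.** **1. The plan's own figure.** Inputs from section 2.2.4: "The estimated intra-individual standard deviation for the difference in XSS score is 2.0"; for the difference to detect, "a difference of at least 1 is assumed to be clinically relevant"; two-sided 0.025 per arm; 80 % power.

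N = σ² × (λα + λβ)² / Δ² = 4 × (2.2414 + 0.8416)² / 1 = 38.02, rounded up to 39. This agrees with the plan: "With 80 % power, two-tailed significance of 2.5 % in every arm, 39 evaluable study persons is needed in every arm". The total is 2 × 39 = 78, and 78/0.8 = 97.5, so 98. The article prints λα as 2.1414, which would give 4 × 2.983² = 35.6, so 36. The stated 39 rests on 2.2414, and the printed value looks like a typing error.

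The primary level is therefore 0.05/2 = 0.025 per arm. With different participants in the two arms, the family-wise rate is 1 − 0.975² = 4.94 %, as intended.

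**2. The same two comparisons at 0.05.** One barrier measure at one visit, tested between feet in each arm: 1 − 0.95² = 9.75 %. This needs no assumed correlation and no assumed list of measures. The same 9.75 % would apply to XSS if section 2.5 were read as overriding section 2.2.4.

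**3. More than one measure or visit.** For k independent tests the chance of at least one p<0.05 under no effect is 1 − 0.95^k.

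| Tests | k | Either direction, if independent |
|---|---|---|
| 3 measures (impedance counted once), day 28, 2 arms | 6 | 26.5 % |
| 4 measures (resistance and capacitance separate), day 28, 2 arms | 8 | 33.7 % |
| 3 measures, both visits, 2 arms | 12 | 46.0 % |
| 4 measures, both visits, 2 arms | 16 | 56.0 % |

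The article does not fix whether impedance counts once or twice, or whether day 14 is tested separately, so each count is an assumption.

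**4. Correlation.** Measures on the same feet will be correlated, and the article gives no values. The 16-test case was simulated under no effect (400,000 draws) with normal test statistics, one common correlation within an arm, and independent arms. The last column counts only significance in favour of the humectant cream, which is 2.5 % per test.

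| Assumed correlation | Either direction | Favouring a humectant cream |
|---|---|---|
| 0 | 56 % | 33 % |
| 0.3 | 51 % | 28 % |
| 0.5 | 44 % | 24 % |
| 0.8 | 29 % | 15 % |
| 0.9 | 23 % | 12 % |
| 0.99 | 13 % | 7 % |
| limit (1) | 9.75 % | 4.94 % |

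For the 6-test case, the either-direction rate is 23.6 % at correlation 0.5 and 18.5 % at 0.8. In favour of a humectant cream it is 1 − 0.975⁶ = 14.1 % if independent.

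**5. Predictor search.** The article gives neither the number of candidates nor the selection rule, so no error rate can be calculated. The point here is one of principle only.

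**The case against.** The strongest reply is that a hierarchy for supportive outcomes is commonly left to a statistical analysis plan, which is not shown, and that a nominal 0.05 for such outcomes is conventional. That is fair, and the absence of a hierarchy is not the point made here. The point is the rule that section 2.5 does state: one level, without exception, for everything listed there.

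Stronger readings are tempting, and the article does not support them:

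- **That the trial has a 29-56 % chance of a false barrier claim.** This range needs 16 tests, correlations from 0.8 down to 0, significance in either direction, and a rule that any one result suffices. The article states no such rule and calls the outcomes supporting. Nor is 29 % a floor: stronger correlation or fewer tests give less.
- **That a chance barrier result would drive product recommendations.** The sentence in the Discussion about recommendations concerns differences in xerosis, which is the primary outcome.
- **That the primary test will be run at 0.05.** Section 2.2.4 is specific about 0.025 and gives its reason. The general sentence in section 2.5 is better read as loosely worded, though it should not be left open.

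Tukey's test does provide some control when the three creams are compared together. It does not reach between-foot tests repeated over measures, visits and arms.

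It may also be said that making one barrier measure a gated key secondary is a matter of preference. That stands, and the step is offered below only as an option.

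**Conclusion.** The point holds in a limited form. As worded, section 2.5 leaves the false-positive rate of the supporting outcomes uncontrolled. The firm figure is 9.75 % for a single barrier measure at a single visit, which rests only on the two arms being separate sets of participants. The larger figures (up to 26.5 % for 6 tests and up to 56 % for 16) depend on assumed test counts and on independence, and they fall as correlation rises. For a false result that favours a humectant cream, the 16-test range is about 15-33 % for correlations from 0.8 to 0.

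None of this invalidates the primary conclusion, provided XSS is tested at 0.025 per arm as section 2.2.4 says. It is an improvement worth making because it costs little.

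**What to change.** 1. Restrict the p<0.05 sentence in section 2.5 so that it does not govern the supporting outcomes, and state there that XSS is tested at two-sided 0.025 per arm, as in section 2.2.4.
2. Report the barrier measures, all day-14 results, EQ-5D-5L, circulation and neuropathy as estimates with confidence intervals and without significance claims. Foot-level measures should be reported as between-foot differences. EQ-5D-5L belongs to the person, so it should be reported as change over the study period.
3. Apply Benjamini-Hochberg control of the false discovery rate within the biomarker set and, separately, within the microbiota set.
4. Label the predictor and model-selection work hypothesis-generating, and report cross-validated or bootstrap performance instead of post-selection p-values.
5. Optional: name one barrier variable at day 28 as key secondary and test it in an arm at 0.025 only if that arm's XSS test is significant at 0.025. Each arm's error then stays at or below 0.025, and the whole family at or below 2 × 0.025 = 5 %.

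Steps 1 to 4 need wording only: no added participants, visits or measurements, and the outcomes keep their secondary status. Step 5 would rank one secondary outcome above the others, which should be documented as a change to the plan. The downside is that fewer secondary results can be called statistically significant.

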
### Reporting

2.6

We will report according to the CONSORT 2010 checklist [29] and CONSORT 2010 Explanation and Elaboration guidelines [30].

### Ethical consideration

2.7

Signed informed consent forms will be obtained from all participants prior to the study start. The study has been approved by the Swedish Medical Products Agency, application number 2022-500907-27-01-SM (substantial modification −1), date of approval 20231101. This RCT is registered the 23 of April 2024, at ClinicalTrials.gov (https://clinicaltrials.gov): Identifier: NCT06427889.

## Discussion

3

The prevalence of diabetes mellitus is increasing in the world, 537 million adults suffer from this condition, and it is estimated to raise [1]. DFU is a devasting complication, ending up in major amputation and shorter life-expectancy for many. Prevention for DFU is therefore a global priority.

Better foot care with hydration may result in healthier feet but also to better vigilance of foot status in persons with diabetes. To be able to show differences in change in skin xerosis when using creams containing humectant compared with humectant-free cream on dry feet in persons with diabetes, might lead to specific recommendations for products that can be used for prevention of DFU. Furthermore, the results of this study can fill the gap of lack of documented effect when using different creams for persons with diabetes.

A potential limitation of this RCT could be that persons with diabetes accepting and attending this study is among those with most healthy feet in a population of diabetes, a well-known phenomenon in population-based screening studies [31]. Consequently, there is a risk that XSS scores at baseline are at the lower range, close to 2, where there is not much room for improvement by intense foot hydration with any of the creams. Determination of XSS scores is not always clear-cut and there may be discrepancies between raters. Therefore, we plan to perform an inter-rater reliability assessment, where twenty randomly selected photographed feet are selected and assessed by two independent dermatologists. The study protocol with at least three visits may for some participants be difficult to comply with, and there is a risk for attrition bias, where persons living far away from the centrally located research centre in Malmö, or elderly with higher degree of comorbidity, drop out from the study. The strengths are the design of two-armed double-blinded RCT, where the patients both feet are randomized, one receiving one of the intervention creams and the contralateral foot by default receiving the comparator cream. In this way, the participants feet act as a perfect matched pair of intervention-control, where patient-related factors are identical. Comprehensive evaluation of skin integrity barrier, microcirculation and neuropathy during the study period will hopefully result in advance in the understanding of disturbances of dry feet in persons with diabetes, and how to counteract.

